## Abstract

**Background:**

Ongoing high neonatal mortality rates (NMRs) represent a global challenge. In 2021, of the 5 million deaths reported worldwide for children under five years of age, 47% were newborns. Pakistan has one of the five highest national NMRs in the world, with an estimated 39 neonatal deaths per 1,000 live births. Reducing newborn deaths requires sustainable, evidence-based, and cost-effective interventions that can be integrated within existing community healthcare infrastructure across regions with high NMR.

**Methods:**

This pragmatic, community-based, parallel-arm, open-label, cluster randomized controlled trial aims to estimate the effect of Lady Health Workers (LHWs) providing an integrated newborn care kit (iNCK) with educational instructions to pregnant women in their third trimester, compared to the local standard of care in Gilgit-Baltistan, Pakistan, on neonatal mortality and other newborn and maternal health outcomes. The iNCK contains a clean birth kit, 4% chlorhexidine topical gel, sunflower oil emollient, a ThermoSpot™ temperature monitoring sticker, a fleece blanket, a click-to-heat reusable warmer, three 200 μg misoprostol tablets, and a pictorial instruction guide and diary. LHWs are also provided with a handheld scale to weigh the newborn. The primary study outcome is neonatal mortality, defined as a newborn death in the first 28 days of life.

**Discussion:**

This study will generate policy-relevant knowledge on the effectiveness of integrating evidence-based maternal and newborn interventions and delivering them directly to pregnant women via existing community health infrastructure, for reducing neonatal mortality and morbidity, in a remote, mountainous area with a high NMR.

**Trial registration:**

NCT04798833, March 15, 2021.

**Supplementary Information:**

The online version contains supplementary material available at 10.1186/s12889-023-17322-y.

## Background

### The context of global and Pakistan specific neonatal mortality

Worldwide, more than 5 million under-five deaths were reported in 2021 of which 47% were newborns (i.e., those between 1 and 28 days of life, inclusive) [1]. Despite global efforts to reduce neonatal deaths, the reduction in mortality is not on track to meet the United Nations 2030 agenda for the Sustainable Development Goals (SDGs) global target of less than 12 neonatal deaths per 1,000 live births [1]. The main causes of neonatal mortality, many of which are preventable, include complications of preterm birth (36%), intrapartum-related complications (24%), infections (16%), and congenital abnormalities (10%) [2]. Further reduction in neonatal mortality requires that effective interventions are scaled up throughout the pre- and postnatal period [3], through innovative platforms and delivery strategies. The scale-up of peri- and postnatal interventions (e.g., skilled delivery attendants, neonatal hypothermia and hyperthermia monitoring, and umbilical cord care) has the potential to reduce newborn deaths related to infectious causes, conditions related to preterm birth, and intrapartum-related complications [3].

Pakistan has one of the highest neonatal mortality rates (NMR) globally. In 2021, reports estimated that 39 out of 1,000 live born newborns died within the first 28 days of life [1]. Pakistan's high NMR is in large part attributable to pervasive health challenges related to poverty and its associated barriers to accessing healthcare. For instance, with its diverse geography there are fewer health facility deliveries in Pakistan relative to other low- and middle-income countries (LMICs) and there is limited access to maternal and newborn healthcare services in rural and remote areas [4, 5]. In rural areas, 82% of pregnant women receive antenatal care (ANC) from healthcare professionals compared to 94% in urban settings [5]. Improving healthcare services in rural areas will require more robust ANC services, maternal education, monitoring programs for pregnancy-related adverse events, and facility deliveries attended by trained personnel [5]. The 2017–18 Pakistan Demographic and Health Surveys found that 41% of mothers in rural areas in Pakistan delivered at home. Furthermore, unsafe home delivery conditions and high-risk newborn practices were found to exacerbate newborn and maternal health risks [5]. These included non-sterile delivery and umbilical cord cutting practices, as well as the application of potentially harmful substances to the baby's skin and umbilical stump (e.g., ghee butter, ash etc.) [6, 7]. In addition to poor neonatal outcomes, Pakistan also has a high maternal mortality ratio (MMR) at 186 per 100,000 live births [8, 9], with the majority of maternal deaths related to postpartum hemorrhage (PPH) [8, 10].

### Healthcare infrastructure in Pakistan

In Pakistan, maternal and child healthcare services are provided through primary, secondary, and tertiary infrastructures that are both publicly and privately funded [11]. The public sector, including hospitals and health units, are well-appointed with trained staff and the necessary health supplies. However, due to factors such as long distances between homes and health facilities, limited working hours for healthcare workers, and financial limitations of both users and providers, the facilities are underutilized, particularly by those living in rural areas [8] which represents 64% of the total population [12]. In 1994, the government of Pakistan launched the Lady Health Worker (LHW) Program, a community health worker program that provides healthcare in rural communities to help address disparities in health services between rural and urban settings in Pakistan [13]. The LHW program aims to enhance access to healthcare services and improve health outcomes [5]. The program recruits LHW candidates from the local community who are between 18 and 45 years of age and have a minimum of eight years of education. LHWs receive training for 15 months in the prevention and treatment of common illnesses and how to deliver education about family planning and maternal and child health in their communities [5, 13]. LHWs are tasked with the following responsibilities: facilitate follow-up for ANC and immunization services, educate women about proper nutrition and disease treatments, promote safe hygienic practices, promote monitoring of children's health through regular home visits, provide family planning supplies, and provide essential preventive and curative health services (e.g., treatment and appropriate referral for children with diarrhea, fever, or respiratory infection) [13]. The LHW mandate is to conduct monthly household visits, including routine visits for pregnant women during their third trimester. Each LHW is responsible for about 150 homes (about 1000–1500 population) and is meant to visit on average 5–7 houses daily [13].

### Rationale

Interventions exist that have been shown to improve maternal and neonatal health and reduce mortality among at-risk populations [3]. However, these interventions are not always accessible or affordable, nor have they been packaged together to be delivered and used by caregivers at their homes. We hypothesize that complementary evidence-based interventions, when packaged together at low cost and delivered through existing community healthcare infrastructure, can lower neonatal and maternal death rates and reduce serious morbidities [3].

Between April 2014 and July 2015, we conducted a pilot community-based, cluster randomized, open-label, controlled intervention trial in Rahim Yar Khan (RYK), Punjab, Pakistan to estimate the effect of an integrated newborn care kit (iNCK) versus the local standard of care (control) on all-cause neonatal mortality [14]. The intervention group received the iNCK via LHWs that visited pregnant women at home during the third trimester of pregnancy. The iNCK included a clean birth kit (CBK) which contained a plastic sheet, cord clamps, sterile blade, gloves, and soap. The iNCK also included 4% chlorhexidine (CHX) topical gel, sunflower oil emollient, a continuous temperature monitoring device called ThermoSpot™, a Mylar reflective blanket, and a reusable instant warmer. We also provided battery-operated scales to LHWs in intervention clusters to measure the newborns' weight. The study enrolled 2663 pregnant women in the intervention group and 2788 pregnant women in the control group [14]. There was no statistically significant difference in NMRs between the intervention and control clusters (risk ratio [RR] 0.83, 95% confidence interval [CI] 0.58–1.18; *p* = 0.30). However, several key findings emerged from the study: (1) using existing community health infrastructure to distribute the iNCK was a feasible delivery mechanism for the intervention; (2) the risk of fever and omphalitis in the intervention clusters was lower compared to the control clusters (RR 0.64, 95% CI 0.47–0.87, *p* = 0.004; and RR 0.68, 95% CI 0.48–0.98, *p* = 0.04, respectively); (3) by using the portable battery-operated weighing scales, LHWs in the intervention group reliably identified a higher proportion of low-birthweight babies among all babies who were delivered at home, which prompted appropriate follow-up care for the newborns (RR 3.48, 95% CI 1.00–12.10; *p* = 0.05); (4) ThermoSpot™ enabled caregivers to identify and act on cases of fever, cold stress, and hypothermia; and, (5) while the iNCK was almost always used, caregiver compliance to specific instructions on how to use the iNCK was low (for example, only 32% and 28% of participants in intervention clusters who used CHX and ThermoSpot™, respectively, started use on the first day of the newborn’s life, as instructed) [14]. Based on the results generated in the RYK pilot trial, further investigation into the implementation of the iNCK is warranted. Key questions that remain unanswered include whether the provision of a pictorial instruction guide will improve caregiver compliance, whether the iNCK can be used to deliver important maternal health interventions, and if the iNCK could have a beneficial impact in a remote, low population density, high mortality setting that has a seasonally cold climate.

### Hypothesis

We hypothesize that using existing LHW networks to distribute the iNCK to pregnant women in Gilgit-Baltistan (GB), a region in northern Pakistan with high NMRs and limited access to facility-based healthcare, as well as enhanced education about correct use of the iNCK, will result in a significant reduction in newborn deaths compared to pregnant women who receive the local standard of care, but no iNCK.

## Methods

### Study setting

The study will be conducted in seven of the fourteen districts of Gilgit-Baltistan (GB): Astore, Diamer, Ghanche, Kharmang, Nagar, Shigar, and Skardu. Gilgit-Baltistan, located in northern Pakistan, bordered by China, Afghanistan, and India [15], has a terrain that is comprised of extensive mountain ranges and glaciers, making its geography and environment starkly different from the rest of Pakistan. Gilgit-Baltistan covers 72,971 km^2 ^and in 2017 had a population of 1.9 million people [15]. Most of the inhabitants of this region live in small, isolated villages that experience harsh weather conditions, particularly during the winter. These conditions further reduce accessibility to healthcare services in the area [15]. The 2017–18 Pakistan Demographic and Health Surveys estimated the NMR and under-five mortality rates in GB to be 47 deaths per 1,000 live births and 76 deaths per 1,000 live births [5], respectively. Additionally, only 64% of pregnant women gave birth with the help of a skilled provider, 78% had at least one problem accessing healthcare (e.g., management of transportation, distance to health facility, not wanting to go alone), and 38% gave birth at home [5].

### Study population

Pregnant women in their third trimester living within participating clusters and intending to be in the study area at the end of the neonatal period will be eligible for enrollment in this study.

### Study design

This study is a pragmatic, open-label, community-based, parallel-arm cluster randomized, controlled trial. Both the iNCK (intervention arm) and local standard of care (control arm) will be delivered to enrolled participants during their third trimester of pregnancy by LHWs. A total of 77 clusters, defined as union councils or sub-union councils with LHW coverage, were randomized, using covariate constrained allocation (using cluster specific estimates of NMR and proportion of health facility deliveries), to either the intervention or control arms. Union councils in Pakistan constitute district subdivisions directly involved in local government administration. These administrative divisions within the seven GB districts of interest were chosen as clusters because LHWs working within the territory of a certain union council provide services only to households within the boundaries of that union council. To obtain 77 clusters and reduce the risk of contamination, some larger union councils were further sub-divided into two or three sub-union councils, each of which was defined as a distinct study cluster based on LHW coverage (i.e., LHW(s) work only within the sub-union area and thus sub-unions could be randomized to different study arms). Union councils and sub-councils were treated as equal units when clusters were randomized to intervention or control groups. Finally, while 78 clusters were initially planned for randomization, one cluster in district Astore had to be excluded, before randomization, due to security concerns and therefore the final allocation was 39 clusters in the intervention arm versus 38 in the control arm.

The study will have two phases: 1) a baseline cross-sectional household survey; and 2) the interventional, cluster randomized trial. The baseline period was completed between June and August 2021, during which time survey data were collected from 10,264 households in the study catchment area. The data collected included information about birth history, stillbirths and neonatal deaths, PPH, maternal deaths, LHW coverage, migration patterns, phone ownership, and household experiences with COVID-19, including how the pandemic affected daily life. The survey was conducted using a two-stage, stratified sampling design and included participants from a representative sample of households from all 77 trial clusters. All data collected were used to ascertain cluster-specific statistics prior to the trial’s implementation such as birth rate, NMR, and the proportion of deliveries taking place at healthcare facilities across the region.

Following the baseline phase of the study and cluster randomization, field teams began to identify all new pregnancies throughout the study catchment area, and during the third trimester of pregnancy, approached these pregnant women to describe the study and collect written or identifying (fingerprint) informed consent for participation. Newly enrolled pregnant women in the intervention clusters are given iNCKs, and LHWs provide instructions on its proper use. Participant enrollment will continue for approximately 26 months to achieve target sample size. Data collectors are fully independent from LHWs and do not participate in any activities undertaken by LHWs in the field or facilities but are not blinded to cluster allocation as they ask questions about iNCK use from only participants in the intervention arm.

### Sample size

With the initially planned 39 clusters per trial arm, an average of 306 live births per cluster (23,868 pregnant women and live-born newborn pairs) is required to achieve 80% statistical power to detect a relative reduction of 25% in all-cause neonatal mortality. Sample size calculations were based on an assumed NMR of 35 newborn deaths per 1,000 live births in control clusters and an estimated intracluster correlation coefficient of 0.002 [16]. Furthermore, to allow for up to 5% attrition due to stillbirths and 10% attrition due to losses to follow-up, we aim to enroll a total of 27,448 pregnant women over a period of approximately 26 months.

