### Statistical analysis plan

Hypothesis testing for this study will be based on a superiority framework and will be conducted at the α = 0.05 significance level. Primary analyses will be conducted using a complete-case, intention-to-treat approach, where participants will be analyzed in the trial arm their cluster was randomized to, irrespective of contamination or adherence to instructions on how to use the iNCK. The unit of analysis will be the individual neonate (neonatal mortality, omphalitis, fever, hypothermia, and healthcare utilization for newborn morbidities) or the individual woman (PPH and healthcare utilization for PPH). Risk ratios for the primary (neonatal mortality) and secondary (omphalitis and PPH) outcomes will be estimated using multivariable modified Poisson regression [29], with generalized estimating equations to account for the clustered design and robust variance estimators to account for multiple births and/or multiple pregnancies during the study period. Analyses of neonatal mortality (the primary outcome) will adjust for newborn sex, antenatal care, and gestational age at birth to improve power and efficiency; calendar time to account for underlying temporal trends (defined as month of birth, setting month of study launch as month 0); and the covariates used in the randomization procedure: GB study district, log cluster-specific baseline NMRs, and the cluster-specific baseline proportion of children delivered at a health facility. Analyses of omphalitis (secondary outcome) will adjust for newborn sex, antenatal care, and GB study district. Analyses of PPH (secondary outcome) will exclude women who delivered via C-section, and will adjust for parity, maternal age, history of prior C-section, history of prior PPH, GB study district, and the cluster-specific baseline proportion of women who reported experiencing PPH. The frequency of hypothermia, cold stress, and fever detected by ThermoSpot™ within the first 14 days of life will be described amongst participants in intervention clusters only, overall and by calendar month to assess seasonality. Finally, the frequency and location of health facility utilization for omphalitis, PPH, hypothermia, and fever will be described using counts and proportions amongst individuals experiencing each respective morbidity and will be stratified by trial arm. The proportion accessing healthcare services by trial arm will be compared using clustered t-tests and modified Poisson regression.

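### The stated sample-size inputs give about 87% power, not 80%; 306 births per cluster needs an input the article does not state

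*Protocol article*

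**What the plan says.** All the main figures stand in the Sample size section of the protocol article.

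- Size and power: "an average of 306 live births per cluster (23,868 pregnant women and live-born newborn pairs) is required to achieve 80% statistical power", for 39 clusters per arm as first planned.
- Effect: "to detect a relative reduction of 25% in all-cause neonatal mortality".
- Basis of the calculation: "assumed NMR of 35 newborn deaths per 1,000 live births in control clusters and an estimated intracluster correlation coefficient of 0.002".
- Enrolment: after an allowance of up to 5% for stillbirths, the text continues "10% attrition due to losses to follow-up, we aim to enroll a total of 27,448 pregnant women".

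The Statistical analysis plan section adds that testing "will be conducted at the α = 0.05 significance level" within a superiority framework; it does not give the sidedness. The Study design section reports that one of 78 planned clusters was excluded before randomisation, so that "the final allocation was 39 clusters in the intervention arm versus 38 in the control arm".

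The article states no coefficient of variation of cluster size, no between-cluster k, no adjustment for interim looks and no other inflation as a sample-size input.

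**The concern.** The paragraph presents the control rate and the ICC as the basis of its calculation and calls 306 births per cluster the number required for 80% power. A reader who puts those inputs through the usual formula gets a clearly different answer. Either an input has been left out or one of the printed figures is wrong, and the article does not let the reader tell which.

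At stake is what the target means. If the printed inputs are the real ones, the trial has a margin of about seven points over 80%. If an unstated allowance is real, the margin is nil, and for the 77 clusters randomised power falls just under 80%.

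The step from 23,868 births to 27,448 women enrolled also looks like a multiplication where a division was needed.

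**Working it through.** **Inputs.** Clusters per arm 39; births per cluster m = 306; p1 = 0.035; p2 = 0.75 × 0.035 = 0.02625; ICC = 0.002; target power 80% (all Sample size). Alpha is 0.05 (Statistical analysis plan). Two-sided testing and equal cluster sizes are my assumptions, since neither is stated.

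**The plan's own total.** 78 × 306 = 23,868. This reproduces.

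**Power at 306 per cluster.**
- Design effect = 1 + (m − 1) × ICC = 1 + 305 × 0.002 = 1.61.
- Births per arm = 39 × 306 = 11,934; effective n = 11,934 / 1.61 = 7,412.
- Variance sum = 0.035 × 0.965 + 0.02625 × 0.97375 = 0.059336.
- SE = √(0.059336 / 7,412) = 0.00283; z = 0.00875 / 0.00283 = 3.09.
- Power = Φ(3.09 − 1.96) = Φ(1.13) = 87.1%.

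**Births per cluster for 80%.**
- Effective n per arm = (1.96 + 0.8416)² × 0.059336 / 0.00875² = about 6,083.
- Solve 39m / (1 + (m − 1) × 0.002) = 6,083, which gives m = 226, or about 17,650 births over 78 clusters. That is 26% below 23,868.

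**Other standard methods.**

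| Method | Power at 306 | Births per cluster for 80% |
|---|---|---|
| Log risk ratio | 86.9% | 229 |
| Arcsine | – | 225 |
| t reference | 86.3% | 235 |
| Continuity correction | 86.1% | 239 |
| One-sided alpha 0.05 | 92.6% | 163 |

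A Hayes–Bennett calculation, with k = √(0.002 × 0.965 / 0.035) = 0.235 derived from the stated ICC, needs 31.7 clusters per arm at m = 306, or 224 births per cluster with 39 clusters. No two-sided variant goes above 239, and a one-sided test moves further from 306.

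**What would bring 306 to 80%, one change at a time.**
- Cluster-size CV of about 0.76: design effect = 1 + ((1 + 0.76²) × 306 − 1) × 0.002 = 1.963; effective n = 11,934 / 1.963 = 6,078; power 80.0%. With a t reference, about 0.70 is enough. A CV of 0.4 would still leave 85%.
- ICC of about 0.0032 (0.0030 with a t reference).
- Hayes–Bennett k of about 0.3: 38.5 clusters per arm, which rounds up to 39.
- Control rate of about 28.9 per 1,000.
- Relative reduction of about 22.8%.
- Two-sided alpha of about 0.025: 303 births per cluster.

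None of these is in the article.

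**Enrolment step.**
- 23,868 × 1.15 = 27,448.2, which is the printed target.
- Dividing losses out would give 23,868 / (0.95 × 0.90) = 27,916, or 23,868 / 0.85 = 28,080.
- Enrolling 27,448 leaves 27,448 × 0.85 = 23,331 to 27,448 × 0.855 = 23,468 births.
- Over 77 clusters this is 303 to 305 per cluster. Against 77 × 306 = 23,562 the gap is 94 to 231 births (0.4% to 1.0%); against 23,868 it is 400 to 537 (1.7% to 2.3%).

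**Power for 39 and 38 clusters at 303 to 305 births each.** About 86.5% on the stated inputs; about 79% if the CV is 0.76.

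**The case against.** The best defence is that a journal article condenses a fuller protocol, and an allowance for unequal clusters may well be stated there. The article speaks of an average cluster size, and its clusters mix whole union councils with subdivided ones. A CV of 0.7 already brings power to 81%, and k = 0.3 gives almost exactly 39 clusters per arm. This stands as a plausible explanation. It does not rescue the paragraph, which names its basis and then gives a requirement about a third larger than that basis supports (306 against 226).

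It can also be said that the error is conservative, since the printed inputs give more than 80%. That stands in full.

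On enrolment, the defence is largely right about size. Measured against the 77 clusters randomised, the gap is at most 1.0%. The stillbirth figure is an upper limit, and the vital-outcomes questionnaire in the Data collection section should reduce loss for the primary outcome. The effect on power is under one point.

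A reader might infer three stronger points that the article does not support:
- *The trial is underpowered or wrongly sized.* Nothing printed shows this; power just under 80% arises only if an unstated allowance is real.
- *The 78-cluster basis is a mistake.* It is openly labelled as the initial plan, and the later exclusion is explained.
- *The target must rise to 28,080.* That figure rests on 78 clusters, and a gap of this size does not call for more enrolment.

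**Conclusion.** The power statement is wrong as written. Under two-sided alpha 0.05 and equal clusters, the stated inputs give about 87% power (86% to 87% across two-sided methods), and 80% needs about 226 births per cluster (224 to 239), not 306. The cause is an unreported or inconsistent input; which one cannot be settled from the article. The CV, ICC and k values that would close the gap are back-calculated illustrations, not findings about this trial.

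The enrolment inflation is a certain but minor slip.

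**What to change.** Reword the Sample size paragraph in one of two ways.

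1. If the printed inputs are complete, state power as about 87% for the planned design and about 86.5% for the 39 and 38 clusters randomised, and stop calling 306 the number required for 80%.
2. If another input led to 306, name it with its value (cluster-size CV, k, a different ICC or other inflation) and give the power for 77 clusters with it. With a CV of 0.76 that would be about 79%.

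In the same paragraph, say that 27,448 women enrolled are expected to give about 23,300 to 23,500 analysed births, or 303 to 305 per cluster over 77 clusters.

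The cost is the rewording of one paragraph and a look at the original calculation. Enrolment, design and analysis do not change.
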